### Data management

During the process of development of the data collection instruments, we will involve representatives of the different stakeholder groups that operate within the community to reflect the community context better. The stakeholders will be invited to participate in a tool development workshop where they will be asked for recommendations on key questions to include or which ideas to query.

Baseline assessments will be conducted with parents when they join the program. The midline data collection will be completed after 6 months of the intervention implementation. The endline survey will be completed after 12 months. Quantitative tools will be used to establish different outcomes among caregivers. Qualitative tools will be used to establish what works and the scalability of the intervention.

We will use structured interviews to capture information on participants’ sociodemographic characteristics such as age, education, and occupation; outcomes of interest such as labor participation and productivity; and other variables such as autonomy, household decision-making, and economic knowledge. We will measure the impact of the use of childcare centers by establishing changes in women’s labor force participation, the number of hours that they work per week, their income, their household income, time allocated to household tasks, and prospects for career advancement.

To further examine the effectiveness of Kidogo’s Program on women’s labor outcomes, what works within the Kidogo model, and aspects that can be scaled up, we will conduct qualitative interviews with about 50 participants at the different levels, including primary caregivers (mainly women), fathers, and center caregivers from both arms, as well as community leaders and policymakers. Towards the end of the intervention implementation, a small number of key informants will be re-interviewed. All qualitative interviews will be audio-recorded with the participants’ permission.

The costing will be carried out from the implementer’s perspective and will include both incremental start-up costs (such as initial training and awareness-raising activities, investment in infrastructure, and material costs) and implementation costs (such as supervisory and continuous monitoring and mentoring activities, materials, personnel, airtime, transport costs). These costs will be captured from both primary and secondary data. Primary data will be captured through a time-use survey to establish self-reported estimates of the time taken to deliver the intervention activities. Secondary data will be obtained from the implementer’s financial records.

Data will be collected using phone-based and in-person interviews in the case where phone interviews will be rendered not appropriate or feasible. Data will be captured electronically by trained field interviewers (FIs) using tablets and will then be uploaded to the SurveyCTO server. Trained team leaders with oversight from the research team will supervise the data collection exercise. Field team leaders will verify the completeness of the data collected by each FI before uploading it to the server. Discrepancies will be addressed as soon as the field team leader together with the field interviewer involved notes them. To improve the integrity of the data, regular spot-checks and sit-ins will be conducted on about 10% of the sample across each FI during data collection.

Similarly, the quality of qualitative data will be enhanced through the recruitment and training of qualified FIs with experience in qualitative data collection. Pretesting of tools and debriefing will be done to ensure the quality of the data. The interviews will be transcribed verbatim by an experienced transcriber and double-coded (about 10% of the transcripts) to ensure consistency in the application of the codes.

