## Abstract

Worldwide, there is a wide gap between what women can contribute to the economy and what they actually contribute. One of the main barriers to women’s engagement in the labor market and productivity at work is the societal expectation that they should take care of their children in addition to meeting the demands of employment. Furthermore, those in informal employment face difficulties due to long working hours and environments that are not appropriate for childcare. To address this, Kidogo runs an innovative “Hub & Spoke” model for low-income communities. Here, we present a study protocol aimed at evaluating whether the provision of quality childcare opportunities for working women through the Kidogo model is feasible and acceptable and whether it contributes to improvements in their incomes and productivity at work. The study reported in this protocol which is currently ongoing, employed a quasi-experimental design with two study arms: primary caregivers who use childcare services were recruited into the intervention (*n* = 170) and comparison groups (*n* = 170). Both groups are being followed up for one year. We are using a mixed-methods approach. Appropriate statistical methods including a difference-in-differences (DID) estimator will be used to analyze the effects of the intervention. We expect that the intervention will improve the quality of childcare services which in turn will improve the incomes of the center providers. We expect that providing improved childcare services will enhance women’s economic empowerment.

**Trial registration:** PACTR202107762759962.

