### Sample size calculation

We anticipate that the intervention will reduce the days of absence among primary caregivers by 50% to 2/24 (8.3%), assuming a rate of absence from work of 17% (4/24) days in a month (unpublished data). A total sample size of 338 (rounded to 340) would be needed to estimate a 50% reduction in the prevalence of absence from work with 80% power, at a 5% significance level, 10% attrition rate, and a design effect of 1.5. We will therefore have approximately 170 primary caregivers in each arm.

The minimum total required sample size for detecting a difference for a two-arm evaluation can be computed as:$$n = \frac{{\left[ {\left( {Z_{1 - \frac{\alpha }{2}}\sqrt {2\underline {pq} } } \right) + Z_{1 - \beta }\sqrt {\left( {P_1\left( {1 - P_1} \right) + P_2\left( {1 - P_2} \right)} \right)} } \right]^2}}{{\left( {P_1 - P_2} \right)^2}}$$where$$\underline p = \frac{{\left( {P_1 + P_2} \right)}}{2}\,{{{\mathrm{and}}}}\,\underline q = 1 - \underline p$$*P*_1_ is the observed proportion of absence and *P*_2_ is the expected proportion of absence after the intervention.

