### Data analysis

Thematic analysis will be used to systematically analyze all qualitative data (in line with the key questions) through five stages: familiarization, defining themes, coding, charting, and interpretation. During the familiarization stage, all transcripts will be read in-depth. We will generate codes by interrogating the data and linking narrative content. In the final stages, we will categorize the codes to identify overarching themes. Members of the research team will then meet to jointly deliberate on the themes in order to develop a codebook that they will use to carry out the thematic analysis independently. The transcripts will be coded using NVivo.

A micro-costing approach will be followed and intervention costs will be derived by entering and analyzing data into a customized costing tool created in MS Excel. Cost data will be entered regularly into the tool, accounting for different timings for cost occurrence. Costs will be allocated to the following categories: personnel, materials, infrastructure, capital, supervision, monitoring and mentoring, airtime, transportation, and joint costs. Capital and investment costs will be annualized over their expected useful life. In addition, donated goods or volunteer time will be appropriately accounted for from an economic perspective. Costing data will be summarized and described for each cost category by the target population (mamapreneurs or caregivers). We will use a single summative worksheet to determine the total cost data for each target population. This will be combined with effect data to estimate the incremental cost-effectiveness of the program. Sensitivity analyses will be conducted on the estimates.

Quantitative data will be cleaned and analyzed using STATA version 16. We will use the difference-in-differences (DID) estimator to compare changes in outcomes (such as labor participation) over time between the intervention and comparison groups to estimate impact. The DID gives a stronger impact estimate than a single difference, which only compares the difference in outcomes between treatment and comparison groups following the intervention. Applying the DID method removes the difference in the outcome between treatment and comparison groups at the baseline.

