We will use propensity score matching (PSM) where intervention group participants will be matched with the comparison based on their likelihood to participate in the intervention given their observable characteristics. Before applying the DID, we will also test the parallel trends assumption, that is, that the trend in outcomes in the intervention and comparison groups was similar before the intervention. We will first identify the indicators of interest. We will then compare the differences in indicator values from before and after the intervention for the intervention group with the same values for the comparison group. We will use a similar DID approach to estimate changes in primary outcomes such as the proportion of women empowered with regards to their participation in the labor market.

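### The sample size and its 80% power rest only on days absent from work, an outcome the article does not name among its aims, impact measures or primary outcomes

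*Protocol article*

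**What the plan says.** The Sample size calculation section uses a single outcome. It begins: "We anticipate that the intervention will reduce the days of absence among primary caregivers by 50% to 2/24 (8.3"%). The starting level is introduced by "assuming a rate of absence from work of 17% (4/24) days in a month (unpublished data"). The required total is given as 338, rounded to 340 or about 170 per arm, "with 80% power, at a 5% significance level, 10% attrition rate, and a design effect of 1.5". No other outcome has a sample size, a power or a target effect.

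Elsewhere the outcomes are different ones:

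- **Abstract.** The evaluation asks about feasibility, acceptability and "whether it contributes to improvements in their incomes and productivity at work".
- **Introduction, specific objectives.** Labor force participation, economic productivity and economic empowerment.
- **Data management.** The interviews cover outcomes of interest, with labor participation and productivity as examples. A separate sentence says how impact will be measured: participation in the labor force and also "the number of hours that they work per week, their income, their household income, time allocated to household tasks, and prospects for career advancement". That sentence is a complete list.
- **Data analysis.** The DID estimator is used "to compare changes in outcomes (such as labor participation) over time", and later for "primary outcomes such as the proportion of women empowered with regards to their participation in the labor market".
- **Discussion.** Participation, productivity and empowerment again.

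Outside the sample size section, absenteeism appears only as background, in the account of workplace childcare under Gender considerations in childcare.

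**The concern.** A power statement is a property of one outcome, one effect and one analysis. Here it is attached to absence from work, while every place that says what the study will measure, compare or call primary names something else. A reader of the eventual report will see a study of 340 women designed with 80% power. If participation, income or empowerment shows no difference, that reader may take it as evidence from an adequately powered comparison, although the article contains no such calculation for those outcomes. The same effect data are to feed the cost-effectiveness estimate and policy advice.

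The listed outcomes cannot stand in for absence. Weekly hours do not reveal days missed, because a missed day can be made up by longer hours on other days.

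**Working it through.** **1. Where absence is named.**

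| Place | Outcomes named | Absence named? |
|---|---|---|
| Abstract (aims) | incomes, productivity at work | no |
| Introduction (objectives) | participation, productivity, empowerment | no |
| Sample size calculation | days absent from work | yes, the only outcome |
| Data management, interview content | participation, productivity (examples) | no |
| Data management, impact measures | participation, hours, own and household income, household-task time, career prospects (complete list) | no |
| Data analysis, DID | labor participation (example) | no |
| Data analysis, primary | proportion of women empowered (example) | no |

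**2. The plan's own figure.** Inputs from the sample size section: P1 = 4/24 (written as 17%), P2 = 2/24 (8.3%), 80% power, 5% two-sided (the printed formula uses Z at 1 − α/2), design effect 1.5, attrition 10%.

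n = [1.96 × √(2p̄q̄) + 0.842 × √(P1(1−P1) + P2(1−P2))]² / (P1−P2)²

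- With 4/24 v 2/24, p̄ = 0.125: [1.96 × 0.4677 + 0.842 × 0.4640]² / 0.0833² ≈ 246.1, so 247.
- With 0.17 v 0.083, p̄ = 0.1265: 228.

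This formula gives the number in each arm, although the article labels it a total. After inflation, 247 × 1.5 / 0.9 ≈ 412 per arm (about 823 in total), or 228 × 1.5 / 0.9 = 380 per arm (760 in total). The stated 338 is not reproduced. The nearest values come from reading a per-arm number as the total: 228 × 1.5 = 342 with no attrition allowance, or 202 × 1.5 / 0.9 ≈ 337 for a one-sided test with continuity correction.

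**3. Power for absence at 170 per arm.** Effective women per arm = 170 × 0.9 / 1.5 = 102.

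Power = Φ{[|P1−P2| × √102 − 1.96 × √(2p̄q̄)] / √(P1(1−P1) + P2(1−P2))}

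- 4/24 v 2/24: (0.8416 − 0.9167) / 0.4640 = −0.16, so about 44%.
- 0.17 v 0.083: (0.8787 − 0.9214) / 0.4661 = −0.09, so about 46%.

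Both treat absence as a per-woman proportion, as the plan does.

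**4. What 102 effective women per arm could detect on other outcomes.** The article gives no baseline rate, SD, correlation or target effect for them, so these figures illustrate scale under assumptions (80% power, two-sided 5%, the same design effect and attrition).

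- Continuous outcome, simple endline contrast: (1.96 + 0.842) × √(2/102) = 0.39 SD.
- Continuous outcome, DID with baseline-endline correlation r: 0.392 × √(2(1−r)). For r = 0.3, 0.392 × 1.183 = 0.46 SD; for r = 0.7, 0.392 × 0.775 = 0.30 SD.
- Proportion, simple endline contrast by the printed formula: an increase of about 19, 18, 16 or 13 points from assumed comparison rates of 50%, 60%, 70% or 80%.

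**The case against.** The strongest reply is that the outcome statements are mostly open. The interview content, the DID outcomes and the primary outcomes are each introduced by way of example, and only the impact-measures sentence reads as complete. Productivity is an aim, an objective, an interview outcome and the achievements dimension in the Discussion, and it is never defined. Absence is a natural productivity item, and the background section mentions lower absenteeism beside better employee performance. The questionnaires are not shown, and Data management describes them as still to be developed with stakeholders. Item-level content is the kind of detail an article leaves to its full protocol.

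This stands against a stronger reading. A reader might infer that absence will not be collected, that no baseline value exists and that the DID on absence cannot be run. The documents do not support that. They show only that absence is not named.

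It does not rescue the power statement. The article itself gives a sizing outcome, a list of impact measures and an example of a primary outcome, and they do not agree. That is a contradiction in the text rather than a detail left to another document. Even if absence is collected under productivity, nothing identifies it as an outcome on which the study will conclude.

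A second fair point is that the 0.39 SD and the 13 to 19 points come from a simple endline contrast under assumed rates, while the plan is DID. They are not figures for the planned estimator and should not be copied into the protocol as such.

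**Conclusion.** The point holds in this form: the 340 women and the 80% power come solely from days absent from work, and the article does not name absence as an aim, objective, impact measure, DID outcome or primary outcome. The stated power therefore applies to no outcome named for the conclusion, and null results on participation, income or empowerment could be misread. This rests on the text alone and needs no assumption about the questionnaires. It does not establish that absence goes unmeasured.

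On size, 170 per arm gives about 44 to 46% power for absence itself under the plan's own inputs and printed formula, so naming absence as primary would not by itself make the 80% true. For the outcomes that are named, the documents do not allow power to be computed. The detectable differences above assume that a design effect of 1.5 and 10% loss carry over to those outcomes, and rest on the stated correlations and comparison rates.

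**What to change.** Choose one of two routes.

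(a) If absence is the intended primary outcome, list days of work missed in the past month among the measured outcomes in Data management, at baseline, midline and endline, and name it in Data analysis as the primary DID outcome. Replace the 80% with the power that 170 per arm gives under the plan's inputs, about 44 to 46%, and say that this treats absence as a per-woman proportion. Retaining 80% under those inputs would instead need about 380 to 412 per arm.

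(b) If absence was not collected at baseline (the Abstract says the study is under way), delete the 80% claim. State the detectable difference for the outcome actually called primary, under the planned DID, with its assumed baseline rate or SD and its baseline-endline correlation. For a continuous outcome, the illustration above gives about 0.46 to 0.30 SD for correlations of 0.3 to 0.7.

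In either case, say whether productivity includes absence. The cost is one or two interview items and some protocol wording, or a less favorable power statement. No extra participants are needed.

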### Data analysis

Thematic analysis will be used to systematically analyze all qualitative data (in line with the key questions) through five stages: familiarization, defining themes, coding, charting, and interpretation. During the familiarization stage, all transcripts will be read in-depth. We will generate codes by interrogating the data and linking narrative content. In the final stages, we will categorize the codes to identify overarching themes. Members of the research team will then meet to jointly deliberate on the themes in order to develop a codebook that they will use to carry out the thematic analysis independently. The transcripts will be coded using NVivo.

A micro-costing approach will be followed and intervention costs will be derived by entering and analyzing data into a customized costing tool created in MS Excel. Cost data will be entered regularly into the tool, accounting for different timings for cost occurrence. Costs will be allocated to the following categories: personnel, materials, infrastructure, capital, supervision, monitoring and mentoring, airtime, transportation, and joint costs. Capital and investment costs will be annualized over their expected useful life. In addition, donated goods or volunteer time will be appropriately accounted for from an economic perspective. Costing data will be summarized and described for each cost category by the target population (mamapreneurs or caregivers). We will use a single summative worksheet to determine the total cost data for each target population. This will be combined with effect data to estimate the incremental cost-effectiveness of the program. Sensitivity analyses will be conducted on the estimates.

Quantitative data will be cleaned and analyzed using STATA version 16. We will use the difference-in-differences (DID) estimator to compare changes in outcomes (such as labor participation) over time between the intervention and comparison groups to estimate impact. The DID gives a stronger impact estimate than a single difference, which only compares the difference in outcomes between treatment and comparison groups following the intervention. Applying the DID method removes the difference in the outcome between treatment and comparison groups at the baseline.

We will use propensity score matching (PSM) where intervention group participants will be matched with the comparison based on their likelihood to participate in the intervention given their observable characteristics. Before applying the DID, we will also test the parallel trends assumption, that is, that the trend in outcomes in the intervention and comparison groups was similar before the intervention. We will first identify the indicators of interest. We will then compare the differences in indicator values from before and after the intervention for the intervention group with the same values for the comparison group. We will use a similar DID approach to estimate changes in primary outcomes such as the proportion of women empowered with regards to their participation in the labor market.

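### The article promises a test of parallel pre-intervention trends, but the data it describes contain only one pre-intervention measurement, so the test cannot be computed from them

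*Protocol article*

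**What the plan says.** The Data analysis section names the impact estimator: "We will use the difference-in-differences (DID) estimator to compare changes in outcomes (such as labor participation) over time" between the two arms. It then commits to a diagnostic step: "Before applying the DID, we will also test the parallel trends assumption, that is, that the trend in outcomes". The same sentence goes on to fix the period that this test refers to, namely that the trend "in the intervention and comparison groups was similar before the intervention". It also describes DID correctly as a method that deals with baseline differences: "Applying the DID method removes the difference in the outcome between treatment and comparison groups at the baseline". Propensity score matching on observed characteristics is planned as well.

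The measurement schedule is in the Data management section:

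- Baseline: "Baseline assessments will be conducted with parents when they join the program".
- Midline: "The midline data collection will be completed after 6 months of the intervention implementation".
- Endline: "The endline survey will be completed after 12 months".

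The Abstract agrees with this schedule: "Both groups are being followed up for one year". The only secondary data source named is the implementer's financial records, and these serve the costing work. The article mentions no earlier survey, no recall of past outcomes and no outside outcome series.

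**The concern.** The promised test concerns a trend over a period before the intervention, while the schedule gives a single point in that period. The analysts would have to leave the test out or put something else in its place and report it under the same name. In either case a reader of the results could believe that the assumption behind the main estimate had been checked when it had not.

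This matters because DID is the named impact estimator and the effect data go on into the cost-effectiveness estimate. According to the Study design and Study participants sections, centers and primary caregivers are selected purposively. Under the Description of the intervention, spokes also depend on the willingness of the center to take part. Selection of this kind can bring together groups whose work and income were already moving differently, and subtracting baseline does not remove such a difference.

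**Working it through.** There is no published figure to reproduce here. The check is a count of time points, followed by the algebra of what they identify.

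**1. Waves (Data management section).** Before the intervention: 1 (baseline). After its start: 2 (6 months and 12 months).

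**2. Can a difference in pre-intervention trend be estimated?** Write the pre-intervention mean outcome as

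mean = constant + group + time + group × time,

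where the last coefficient is the differential pre-trend. All four coefficients are estimable only if the design matrix has rank 4.

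- One pre-intervention wave (time 0): the rows are (1, 0, 0, 0) and (1, 1, 0, 0), so the rank is 2 of 4. The time and group × time columns are all zero, and the differential trend is not estimable at any sample size.
- Two pre-intervention waves (for example −6 and 0 months): rank 4 of 4.
- Three pre-intervention waves (−12, −6 and 0 months): rank 4 of 4.

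The minimum is therefore two pre-intervention points in each arm.

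**3. Can the available data stand in for the test?** Let the arms differ by d at baseline, let δ be the differential background trend per month, and let τ(t) be the true effect at month t. The DID contrasts against baseline are

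- midline: D6 = τ(6) + 6δ
- endline: D12 = τ(12) + 12δ

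The baseline difference d cancels, as the article says, but δ does not. A comparison of baseline levels tells us about d and nothing about δ. The midline-to-endline change gives D12 − D6 = τ(12) − τ(6) + 6δ, in which drift is mixed with any further growth or decline of the effect. There are two equations and three unknowns. They could be solved for δ only by assuming τ(6) = τ(12), which is hard to assume for an intervention whose training program for center providers runs for 9 months, past the midline survey.

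**4. Scale, for illustration only.** The Sample size calculation section assumes that absence falls from 4/24 to 2/24 days per month.

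- Hypothesised effect: 4/24 − 2/24 = 2/24 = 8.3 percentage points, or 2 days.
- Drift that equals it over 12 months: 8.33/12 = 0.69 percentage points per month, or 2/12 = 0.17 days per month.

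With τ(12) = 0 and a drift of this size in the favourable direction, D12 would equal the full hypothesised effect.

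**The case against.** The strongest reply is that the article lists survey waves and not the questionnaire. One baseline interview can hold recall questions about earlier months, and a condensed article need not print its instruments. That is fair as far as it goes, and it limits the claim: the test cannot be computed from the data that the article describes. A reader might infer that it is impossible under any source the team may hold, and the article alone does not establish that. Still, a stated test and a stated schedule that do not fit together are more than missing detail. A later analysis plan would have to name another source or withdraw the test.

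A second reply is that the design already supports the comparison. The Study design section has sites randomly assigned, with a buffer zone, and arms matched on population size and background characteristics; propensity score matching follows in the analysis. A reader might infer that the whole causal claim hangs on the untested assumption alone, and these features show that this is too strong. Their support is partial, however. Participants within sites are chosen purposively, the sites lie in one sub-county of five wards, and matching balances observed characteristics. None of this tests a pre-intervention trend.

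Three further inferences go beyond the text. First, one might read the test as a condition for using DID. The wording gives an order of steps, with no decision rule and no fallback. Second, one might take 0.69 points per month as an estimate of bias. It is only the assumed effect divided by 12, and it uses absence, which the article uses for the sample size but does not name as a DID outcome. Third, because baseline is tied to joining and midline to implementation, one might suspect that baseline follows exposure. Joining ordinarily means enrolment, and the Study site section says the setting was chosen because it had no earlier intervention of this kind, so this is a possibility and not a contradiction.

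**Conclusion.** The concern holds in this form: the article promises a test of pre-intervention trends, and the data it describes have one pre-intervention point per arm, so the differential pre-trend is not estimable (rank 2 of 4). Neither the baseline comparison nor the later waves can replace it. The conclusion rests on the schedule as printed and on the absence of any described retrospective or external outcome series; it would change only if such a source exists.

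The DID estimator itself remains usable. What changes is what may be concluded from it: parallel trends is an assumption with partial design support, not a tested fact. The size of any resulting bias cannot be derived from the documents.

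**What to change.** 1. Remove the promised test of pre-intervention trends. Alternatively, name an existing data source with at least two pre-intervention time points in each arm and say which outcomes it covers.
2. State that parallel trends is assumed and not tested. Cite random assignment of sites, matching of arms and propensity score matching as partial support only, and say that baseline balance and the midline-to-endline change will not be presented as a test of it.
3. Add a tipping-point sensitivity analysis. For each DID outcome, report the differential monthly trend that would bring the estimate to zero (D12/12 at endline, D6/6 at midline), and the same for the confidence limit nearer to zero. Readers can then judge whether a trend of that size is plausible in this setting.

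New recall items or an additional pre-launch survey are probably too late, since the Abstract reports the study as ongoing with both arms recruited. The fix therefore does not depend on new data. It costs a change of wording, a few lines of analysis code and a more cautious causal claim. Sample, visits and the DID estimator stay as they are.
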